## Abstract

**Background:**

Providing comprehensive and continuous care for patients whose conditions have mental or behavioral components is a central challenge in primary care and an important part of improving universal health coverage. There is a great need for high and routine availability of psychological interventions, but traditional methods for delivering psychotherapy often result in low reach and long wait times. Primary Care Behavioral Health (PCBH) is a method for organizing primary care in which behavioral health staff provide brief, flexible interventions to a large part of the population in active collaboration with other providers. While PCBH holds promise in addressing important challenges, it has not yet been thoroughly evaluated.

**Methods:**

This cluster randomized trial will assess 17 primary care centers (PCCs) that are starting a PCBH implementation process. The PCCs will be divided into two groups, with one starting immediate implementation and the other acting as a control, implementing six months later. The purpose of the study is to strengthen the evidence base for PCBH regarding implementation-, organization-, and patient-level outcomes, taking into consideration that there is a partially dependent relationship between the three levels. Patient outcomes (such as increased daily functioning and reduction of symptoms) may be dependent on organizational changes (such as availability of treatment, waiting times and interprofessional teamwork), which in turn requires change in implementation outcomes (most notably, model fidelity). In addition to the main analysis, five secondary analyses will compare groups based on different combinations of randomization and time periods, specifically before and after each center achieves sufficient PCBH fidelity.

**Discussion:**

A randomized comparison of PCBH and traditional primary care has, to our knowledge, not been made before. While the naturalistic setting and the intricacies of implementation pose certain challenges, we have designed this study in an effort to evaluate the causal effects of PCBH despite these complex aspects. The results of this project will be helpful in guiding decisions on how to organize the delivery of behavioral interventions and psychological treatment within the context of primary care in Sweden and elsewhere.

**Trial registration:**

ClinicalTrials.gov: NCT05335382. Retrospectively registered on March 13th, 2022.

**Supplementary Information:**

The online version contains supplementary material available at 10.1186/s12913-023-10180-9.

## Background

Primary care constitutes a foundation for the healthcare system by providing a first line of somatic and mental care, as well as continuous, long-term management of chronic and complex health problems [1]. Almost half (46%) of all adults experience mental illness over the course of their lifetime, and the majority of these patients are treated in primary care, where up to a third of all visits are related to mental health [2–4]. Mental health conditions substantially reduce functioning [5] and quality of life [6], as well as contributing significantly to sickness absence, productivity loss and unemployment [7, 8]. In addition, there is a strong relationship between mental health and chronic somatic diseases, such as diabetes, obesity, and persistent pain, and many patients have complex health problems with multiple somatic and mental comorbidities as well as social difficulties [9–11]. In addition to the suffering experienced by the individual, these conditions pose an enormous economic burden [12]. It therefore follows that the quality of primary care has direct implications for many patients’ health and daily lives, as well as society at large. As such, the World Health Organization (WHO) has designated the integration of mental health services into primary care a key objective, highlighting its role in achieving universal health coverage [13, 14]. However, the volume and complexity of mental health concerns presenting in primary care currently exceeds its capacity and competence [13, 15, 16]. In Sweden, most primary care centers (PCCs) have introduced on-site clinical psychologists or social workers, and national policies state that early access to psychological treatments is to be prioritized over pharmacological interventions in most cases of mild to moderate mental health problems [17, 18]. However, in many PCCs psychological care is still hard to access, likely because the traditional model for delivering psychotherapy and psychosocial interventions is impossible to scale up enough to meet the need for such treatment [19]. Consequently, Swedish primary care patients rarely receive nonpharmacological interventions for their mental and behavioral health, with only 3% of patients meeting with a psychologist or social worker [20]. On a global scale, the service gap is even more pronounced, with a large proportion of people with mental health conditions receiving no formal care at all [21].

Primary Care Behavioral Health (PCBH) is a team-based model aiming to enhance primary care by integrating behavioral health expertise, with the goal of improving care for the entire clinic population [22]. Interventions within the model focus on behaviors and skills relevant for preventing deleterious somatic and psychological health outcomes and can take many forms, for example as selected interventions from evidence-based cognitive behavioral therapy (CBT) manuals or as interventions specifically designed to be brief, such as Focused Acceptance and Commitment Therapy (FACT) [16, 23–26]. PCBH is characterized by routine delivery of such interventions to a large proportion of patients, with high availability and productivity. It utilizes teamwork and task-sharing between and across professional disciplines to increase flexibility, efficiency, and treatment adherence as well as share knowledge and build consensus among staff. A central part of the model is freeing up resources by providing brief visits, usually no more than 30 min in length, one visit at a time rather than in a planned series of visits. Follow-up is based on a ‘consultant’ rather than a ‘therapist’ approach, where the patient is not followed until the point of remission but until there is some improvement in symptoms or functioning. Treatments are open-ended, meaning that patients can easily book another visit if they need to. For large or resource-intensive patient categories, clinical pathways incorporating group sessions or online interventions are frequently employed. A pragmatic and population-based mindset, where the available resources are used to reach as many patients as possible, permeates the model.

PCBH has gained popularity, likely due to its promise of a much-needed increase in the availability of psychological interventions. Previous research indicates that brief psychotherapeutic interventions within integrated care lead to broad improvements in symptom reduction, functioning and well-being across a multitude of problem areas [23, 25, 27–41]. Studies have also indicated that PCBH is cost-effective [41–47], appreciated by care providers [45, 48–51] as well as patients [48, 50, 52], and that the model can improve access to and reduce wait time for mental health services [53, 54]. However, as of yet, there are no large-scale comparative studies of high quality [55, 56]. Achieving and studying change in primary care can be difficult, especially when implementing complex interventions that require change across multiple levels [57]. This is especially true for PCBH, as most mental health staff lack training in how to effectively adapt to the primary care setting, which complicates implementation and highlights the role of model fidelity in the evaluation of the model [58–60].

## Methods/design

The main purpose of the current project is to strengthen the evidence base for PCBH regarding implementation-, organization-, and patient-level outcomes by conducting the first large-scale randomized study on the model, taking a step toward answering whether the effects of the model are large enough to merit scaling up implementation. The research questions of primary interest are divided into three levels, where outcomes of higher levels are more or less dependent on the lower levels (i.e., patient outcomes may be dependent on organizational outcomes and both are clearly dependent on implementation outcomes; see Fig. 1):

Implementation level:
What is the timeline for partial implementation (FID2) as well as achieving adequate model fidelity (FID3, primary implementation level outcome) in PCCs adopting the PCBH model?How do healthcare staff perceive the acceptability, feasibility, and appropriateness of PCBH, and to what extent do they adhere to the model?What are the observed obstacles and facilitators during implementation?
Organizational level:
Is PCBH superior to traditional Swedish primary care in reducing waiting times (primary organization level outcome) and increasing patient reach?Does PCBH result in shorter treatment lengths and lower costs for staff and resources compared to traditional primary care?Does PCBH improve interprofessional collaboration and staff work environment compared to traditional care?Does PCBH impact medication prescription patterns, sick leave utilization, and patients’ care consumption, thereby influencing related costs?
Patient level:
Is PCBH superior to traditional Swedish primary care in terms of patient outcomes, including everyday functioning (primary patient level outcome), symptoms, quality of life, satisfaction with care, subjective change, and adverse events?If not superior, is PCBH non-inferior to traditional primary care?What methods are used within brief interventions and what strategies do patients adopt after treatment?

The primary comparisons between PCBH and traditional primary care will consider model fidelity at both the organizational and patient levels. The main analysis will compare PCCs randomized to the early implementation arm once they reach satisfactory fidelity with PCCs in the control group.

**Fig. 1 Fig1:**
[figure not shown]
Dependent relationships between levels of outcomes

### Design and overall procedure

The project is a cluster-randomized clinical trial following Good Clinical Practice (GCP) principles. Standard Operating Procedures will be developed for key routines, and digital Client Report Files will be stored in the study technical platform provided by Karolinska Core Facilities. Study coordinators will primarily monitor data quality and routines internally. This protocol was devised according to the SPIRIT reporting guidelines [61]. Any substantial amendments to this protocol will be tracked, dated and described in trial reports.

Data will be collected at Närhälsan, the provider of public primary care in Västra Götaland, Sweden, consisting of 104 PCCs in both urban and rural areas. This project studies a naturalistic implementation effort initiated by Närhälsan, with external trainers and supervisors procured by the organization. The study will utilize a cluster-randomized design, randomly assigning PCCs to either implement PCBH immediately (EARLY) during the first 5–9-month period or act as control centers and implement PCBH during the second period (DELAYED). Period 1 starts when all PCCs in the EARLY group have scheduled starting dates during on-site consultations. Period 2 begins when all PCCs in the DELAYED group have done the same, within 5 to 9 months after the start of Period 1. Provided sufficient project resources, period 2 can be lengthened to allow for continued data collection. Patient measures will be collected up to two months before Period 1, and some organizational measures up to one year in advance, establishing a baseline for each PCC. As the project, due to the naturalistic approach, has little direct control over how well a PCC implements PCBH, the analysis plan covers several scenarios where varying degrees of model fidelity are considered (see Data analysis plan).

### Participating primary care centers and randomization

The project includes 8 subregions within Närhälsan, each providing 1–4 PCCs that do not currently adhere to PCBH principles but are willing to implement the model and be part of the randomization process. No other inclusion or exclusion criteria were applied. Basic characteristics of PCCs will be collected through semi-structured interviews at the beginning of the study. This includes information such as the number of listed patients, sociodemographic indexes, number of mental health staff and their training, whether there is and the size of any queues for mental health treatment, as well as details about triage, referrals, and teamwork routines.

In total, 17 PCCs serving a total of 187 000 patients have chosen to participate. For a list of sites, see ClinicalTrials.gov registration. Cluster randomization between the EARLY and DELAYED arms will be conducted using the online tool randomization.com in a 1:1 ratio. The Karolinska Trial Alliance (KTA), an independent unit, performs the randomization separately for each subregion without block division to ensure at least one PCC in the EARLY arm per subregion. If the distribution of PCCs between study arms deviates by more than one, KTA will repeat the randomization until the distribution is balanced or deviates by one. Only the results will be shared with the researchers. Any additional PCCs joining the project after subregion randomization but before the start of implementation period 1 will be randomized by KTA using list randomization with even blocks of random sizes determined by KTA and not shared with researchers.

### Participant recruitment and power analysis

All patients aged 18 and above who are suitable for behavioral or mental health interventions, regardless of diagnoses and concomitant care, will be invited to participate in the study. This inclusive approach aligns with the naturalistic setting and the broad scope of the PCBH model. Trained research assistants will identify and contact potential participants, providing digital access to written information and a consent form. Participants will be kept blind to the implementation status of PCBH in their respective PCCs, as all are only informed that the study aims to evaluate and improve mental health treatment in primary care.

We estimate that 70% of patients identified and informed about the study will consent to participate. Power calculations aiming for a power of 90% in detecting a difference of *d* = 0.4 on a superiority test on the primary patient outcome, adjusted for the lower power in a cluster randomized design with 8 PCCs in one group and 9 in the other, estimating the Intracluster Correlation Coefficient (ICC) to 0.01 [62] and a follow-up response rate of 80%, indicate that a total of 476 patients need to be analyzed, 595 patients recruited, and 850 identified and informed.

If PCBH’s superiority over traditional care is not established, a secondary aim is to determine if PCBH is non-inferior. Since there is currently no empirically based definition of the minimal clinically important difference for WHODAS-12 [63] and even less so for the 8-item version we use (see below), we will adopt a conservative non-inferiority margin based on recommendations for a minimally relevant clinical effect for depression, with a Cohen’s *d* of 0.24 [64]. To achieve 80% power with the same ICC as mentioned earlier, this analysis would require the inclusion of 815 patients, with a total of 1455 patients identified and informed. However, this is a secondary objective dependent on resource availability. In case the expected rates of inclusion or follow-up responses are lower than anticipated, we will consider extending the implementation periods to increase participant enrollment.

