#### Sociodemographic and clinical data

Social and economic status, education, profession, and employment/activity status will be collected through self-report. The main reason for the visit, the duration of the problem, other health concerns, concomitant care, care consumption, ICD-10 diagnoses and medications will be captured through self-reports and medical records.

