#### Primary Care Behavioral Health (PCBH)

An obstacle to high quality PCBH research is that there is a variation in the understanding of the aim and key strategies of the model [59]. In this project, a version of the PCBH model adjusted for the Swedish health care system [15] will be used. The focus of the implementation effort is to increase access and decrease wait times for mental health interventions as well as increase collaboration between psychologists/social workers and medical staff. The planned changes include introducing direct triage, same-day appointments, clinical pathways, and a stepped care model for interventions as well as shortening appointment lengths and increasing productivity. Importantly, the typical PCBH routine of ‘warm hand-offs’ (patients being offered a visit with a mental health professional directly after a visit with a primary care physician) [22] will not be emphasized, as Swedish health care increasingly leans on direct triage, where the physician visit is postponed or replaced entirely [78]. Another aim is to increase the efficiency of interprofessional collaboration by defining and clarifying the role of the mental health staff, educating other professions in when and how to utilize their services as well as introducing a common language and mindset for discussing mental health issues with both patients and colleagues. Routine coordination, efforts to reach a shared understanding among staff and quick ‘curbside consultations’ will be emphasized over scheduled team conferences. Mental health staff will be taught to assess patients’ problems through a contextual rather than a medical model of mental health and administer brief interventions adapted to the patients’ problem and life situation, as described in the introduction. All mental health staff will receive three days of training followed by six 4-hour supervision sessions over the course of six months. Training and supervision will focus on both organizational and clinical aspects of the model. Additional support for individual PCCs will be considered in the case of low model fidelity. A local implementation group will be established at each PCC, consisting of all mental health staff, managers as well as representatives for physicians, nurses, and other relevant occupations. All other staff will receive 2 hours of training. All training and supervision will be conducted by an external part. One of the authors ([name]) will together with research assistants oversee adherence by monitoring implementation outcomes (see Model adherence, obstacles, and facilitators) and giving feedback and recommendations to PCC managers and PCBH supervisors. No additional auditing is planned.

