### Data analysis plan

We are planning to conduct one main analysis for each of the primary outcomes at each level, a range of explorative and longitudinal analyses for the implementation-level outcomes, and several secondary analyses for the organizational- and patient-level outcomes. Primarily, we aim to confirm that the EARLY arm reaches adequate fidelity level faster than the DELAYED arm and to capture the randomized controlled effects of PCBH on organization- and patient-level outcomes when it has reached adequate model fidelity during the first implementation period (corresponding to an implemented-per-protocol perspective). We also want to evaluate the controlled effects of intending to implement PCBH regardless of what level of fidelity each PCC reaches (corresponding to an intent-to-implement perspective) and the non-controlled (i.e., not comparing the randomized groups) relation between reaching adequate model fidelity and outcomes (corresponding to an adherence-effect or dose-response perspective). No interim analyses are planned.

Implemented-per-protocol analyses:

PCCs in EARLY, from when they have reached FID3, compared to all PCCs in DELAYED, during period 1 (main analysis).As (1), but also including data from period 2 in EARLY (but not in DELAYED), to control for the event of PCCs needing extended time to reach FID3, thus lowering the power of the main analysis.

Intent-to-implement analyses:

3.All PCCs regardless of model fidelity in EARLY compared to all PCCs in DELAYED during period 1.4.As (3), but for periods 1 and 2.

Adherence-response analyses (not controlled by randomization):

5.All PCCs, regardless of arm, when in FID3 during period 1 or 2, compared to PCCs in DELAYED during period 1.6.As (5), but compared to all PCCs before they reach FID3.

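### Patients are identified after centre allocation by research assistants not stated to be blind, under a care model meant to widen reach, so case-mix may differ between arms; the patient-level models should condition on baseline scores already collected

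*Protocol article*

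**What the plan says.** **Order of events.** *Design and overall procedure* describes "randomly assigning PCCs to either implement PCBH immediately (EARLY) during the first 5–9-month period or act as control centers". Patients are then recruited at centres whose arm is already set.

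**Eligibility.** *Participant recruitment and power analysis* states one rule for both arms: "All patients aged 18 and above who are suitable for behavioral or mental health interventions, regardless of diagnoses and concomitant care, will be invited". The article does not define suitability further.

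**Who identifies patients.** The same section says: "Trained research assistants will identify and contact potential participants, providing digital access to written information and a consent form". The only blinding described is of patients: "Participants will be kept blind to the implementation status of PCBH in their respective PCCs". In the section *Primary Care Behavioral Health (PCBH)*, one of the authors "will together with research assistants oversee adherence by monitoring implementation outcomes".

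**Access under each model.** *Background* says "PCBH is characterized by routine delivery of such interventions to a large proportion of patients, with high availability and productivity". The PCBH section plans direct triage and same-day appointments. *Care as usual (CAU)* describes written physician referral without direct triage, low reach and queues. Whether PCBH increases patient reach is itself a research question.

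**Main contrast.** *Data analysis plan*, analysis 1: "PCCs in EARLY, from when they have reached FID3, compared to all PCCs in DELAYED", in period 1. Analyses 3 and 4 use all EARLY centres whatever their fidelity.

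**Models and baseline data.** *Statistical tests* names hierarchical linear models and GEE with patients nested in centres. *Sensitivity analyses* varies the fidelity cut-off and examines the timing of the pre-measure. Table 1 places PHQ-9 and GAD-7 at the initial visit, and "The main reason for the visit, the duration of the problem, other health concerns, concomitant care, care consumption, ICD-10 diagnoses and medications will be captured" from self-report and medical records.

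**The concern.** Randomising centres balances the populations that the centres serve, apart from chance. It does not balance the patients enrolled afterwards if the allocated care model affects who is identified. Here the intervention is intended to bring more people to mental health care by a shorter route. If it succeeds, the pool from which research assistants pick suitable patients may differ between arms. The main analysis may sharpen this, because it samples EARLY only once fidelity is adequate, when access should have changed most.

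The patient-level primary outcome is at stake. If the additional EARLY patients are milder, they will show better WHODAS functioning at 12 weeks without any treatment effect. If the result is read as change from baseline, the same patients have less room to improve and a real benefit may be hidden. Both the superiority answer and the fallback non-inferiority answer are exposed, and the form of the model decides the direction of the error.

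**Working it through.** **1. Do the planned safeguards reach this bias?**

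- Nesting by centre corrects the variance. It does not shift a biased mean difference.
- Patient blinding concerns how patients respond, not who is identified.
- The fidelity cut-off analysis changes which EARLY patients count as treated. The timing analysis asks whether the pre-measure came before or after the first visit. Neither compares who was recruited.
- Intent-to-implement analyses 3 and 4 remove the post-FID3 restriction but keep the difference in route to care.

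**2. Inputs from the article.** 476 patients analysed, 17 centres (8 and 9), ICC 0.01, target d = 0.40, non-inferiority margin d = 0.24.

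The onward recruitment steps reproduce: 476/0.8 = 595 and 595/0.7 = 850. The figure 476 does not: at ICC 0.01 and 90% power (two-sided 5% assumed) I get about 308 by normal approximation and about 374 with t on 15 df. That is a separate matter on the conservative side. I use 476 below only to obtain a standard error.

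**3. Assumptions, none from the article.** Of the EARLY patients, 20% to 30% are additional patients who would not have been reached under usual care. They are 0.5 to 1.0 SD milder. The baseline-to-12-week correlation r is 0.5 to 0.6. SDs are equal at both times and there is no treatment effect.

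**4. Baseline shift D = share × severity gap.**

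- Low: 0.2 × 0.5 = 0.10 SD
- High: 0.3 × 1.0 = 0.30 SD

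**5. Bias by type of analysis.**

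| Analysis | Formula | Low | High |
|---|---|---|---|
| 12-week score alone | r × D | 0.5 × 0.10 = 0.05 | 0.6 × 0.30 = 0.18 |
| Change score (opposite direction) | (1 − r) × D | 0.4 × 0.10 = 0.04 | 0.5 × 0.30 = 0.15 |
| Baseline as covariate | 0 if the shift acts only through the measured baseline | 0 | 0 |

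For the 12-week score alone, the bias is 0.05/0.40 = 12.5% to 0.18/0.40 = 45% of the target, and 0.05/0.24 = 21% to 0.18/0.24 = 75% of the margin.

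**6. Effect on the superiority test.** With 476/17 = 28 patients per centre, the design effect is 1 + 27 × 0.01 = 1.27. SE = √[1.27 × (1/224 + 1/252)] = 0.103 SD. By normal approximation, the two-sided type I error of an unadjusted 12-week comparison is about 8% at a bias of 0.05 and 41% at 0.18, against a nominal 5%. An intermediate case, D = 0.2 and r = 0.5, gives a bias of 0.10 and about 16%.

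**7. Why the form of adjustment matters.** A hierarchical model with a free group-by-time term estimates a difference in change, so it carries the second row of the table. Having the pre-measure in the data set is not enough; it has to be conditioned on.

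**The case against.** The strongest reply is that the article documents no imbalance. Eligibility is worded identically for both arms, and *Patient outcomes* places the pre-measure around first contact with the centre, not at the mental health visit, which may limit any difference. This stands. A reader might infer that the arms do recruit different patients, or that EARLY patients will be milder. The text supports neither as fact; it supports only a credible route to a difference. Nor does it say that the centres judge suitability, since research assistants identify the patients.

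Second, covariates are commonly left to a SAP, which is not shown. This also stands: a missing covariate list is not an error, and the article does not commit to an unadjusted comparison. The point rests on what is fixed, namely recruitment after allocation, recruiters not stated to be blind, a model intended to change access, and a post-FID3 contrast.

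Third, the magnitudes are assumed, and the top of each range needs every input at its extreme. That is correct, and they should be read as a range.

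Fourth, adjustment is not clean. Some pre-measures follow the first visit, and same-day appointments are a PCBH feature, so the baseline may already carry some effect of care. That stands as a caveat and shapes the fix.

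A reader might also conclude that the invitation rule should be changed. Period 1 began in January 2022 and period 2 begins within 5 to 9 months, so period 1 ended by about October 2022. A new rule could not affect the main analysis and would make recruitment differ between periods.

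**Conclusion.** The concern holds as a risk of identification bias that the stated design leaves open in the patient-level comparison. Under the assumptions shown, it is worth 0.05 to 0.18 SD in an unadjusted 12-week comparison and 0.04 to 0.15 SD in the opposite direction in a change-score reading. The upper part of either range would matter for both the 0.40 target and the 0.24 margin; the lower end would be modest. The share of additional patients, their severity and the correlation are all assumed, as is the direction. Confidence is medium. The documents do not show that the arms differ or that adjustment has been ruled out. They do show that randomising centres cannot by itself guarantee comparable patients here.

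**What to change.** Before the patient-level data are analysed:

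1. In the superiority and non-inferiority models, enter pre-measure 8-item WHODAS as a covariate, not only through change or a group-by-time term. Add PHQ-9, GAD-7, main reason for visit and problem duration.
2. Repeat the adjusted analysis in patients whose pre-measure came before the first visit.
3. Report by arm and period the numbers identified, invited and consenting, with baseline profiles. Use the patient data from up to two months before period 1 to check whether case-mix changed within centres.
4. Interpret the patient-level effect in the light of item 3. If profiles diverge, say that adjustment covers only measured differences.

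Leave the invitation rule as it is.

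**Cost.** Analysis wording and some tabulation; the covariates are already collected and should add precision. The model loses a few degrees of freedom, unmeasured case-mix remains, and some true effect may be adjusted away where the pre-measure follows the first visit. The restricted analysis in item 2 examines that last problem with fewer patients.

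### The stated 90% power with 476 analysed assumes that all 17 centres contribute in full, so it is not the power of the FID3-restricted main analysis

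*Protocol article*

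**What the plan says.** The Protocol article, section Participant recruitment and power analysis, sets a target of 90% power for a standardised difference of 0.4 in everyday functioning. The calculation is described as "adjusted for the lower power in a cluster randomized design with 8 PCCs in one group and 9 in the other". Its other inputs are an ICC of 0.01 and an expected 80% of participants responding at follow-up. The section's conclusion is that these calculations "indicate that a total of 476 patients need to be analyzed, 595 patients recruited, and 850 identified and informed". The 850 also uses the 70% consent rate in the same section. No significance level, sidedness or test is given.

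The opening of Methods/design and the Data analysis plan both fix the main analysis. It compares EARLY centres, counted from when they reach FID3, with all DELAYED centres in period 1. Analysis 2 adds EARLY data from period 2 "to control for the event of PCCs needing extended time to reach FID3, thus lowering the power of the main analysis". Analysis 3 compares all EARLY with all DELAYED centres in period 1, whatever their fidelity.

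On timing, Design and overall procedure gives period 1 a length of 5 to 9 months. The section on the PCBH model describes "three days of training followed by six 4-hour supervision sessions over the course of six months".

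**The concern.** The power paragraph and the main analysis describe different sets of patients. The first counts 8 + 9 centres and everyone analysed in them. The second drops every EARLY patient seen before FID3 and every EARLY centre that does not reach FID3 in period 1. The Data analysis plan acknowledges that late FID3 costs power, but the power figure is not adjusted and is not tied to a particular analysis.

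If this stands, a null main result on everyday functioning could be read as coming from a 90%-powered comparison when it did not. The 595 and 850 targets could also be met with few EARLY patients eligible for the main analysis.

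**Working it through.** **Inputs from the protocol.** d = 0.4 (SD 1), power 90%, ICC 0.01, 8 and 9 centres, 80% response, 70% consent, 476 / 595 / 850.

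**Assumptions, not in the protocol.** Two-sided 5% (alternatives below); equal centre sizes, 476/17 = 28; EARLY is the 8-centre arm (8 × 28 = 224 EARLY, 9 × 28 = 252 DELAYED); the number of EARLY centres at FID3 and the share of their patients seen after it.

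**1. The inflation chain.** 476/0.8 = 595 and 595/0.7 = 850. Both are exact, so nothing is left for patients excluded by the FID3 rule.

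**2. The 476 itself.** With k centres of m patients in each arm,

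Var = (ICC + (1 − ICC)/m1)/k1 + (ICC + (1 − ICC)/m2)/k2.

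The test uses either normal quantiles or a noncentral t with k1 + k2 − 2 df.

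- Two-sided 5%, normal: the SE must be 0.4/(1.960 + 1.282) = 0.1234, so Var = 0.01523. Dividing by 1/8 + 1/9 = 0.2361 gives 0.0645 per centre. Then 0.99/m = 0.0545, m = 18.2 and N = 309.
- Two-sided 5%, t with 15 df: N = 364.
- At N = 476, m = 28: 0.01 + 0.99/28 = 0.04536; Var = 0.04536/8 + 0.04536/9 = 0.01071; SE = 0.1035; 0.4/0.1035 = 3.87. Power is 95.0% (t) or 97.2% (normal).

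Several unstated settings do lead to 476. Two-sided 2.5% with t on 15 df needs 28 per centre, 28 × 17 = 476, with power 90.2%. Two-sided 1% with normal quantiles also needs 28 per centre. Two-sided 5% with t at 95% power gives 475. The listed inputs do not show which, if any, was used.

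**3. Power under the main-analysis rule.** DELAYED stays at 9 × 28. EARLY becomes k1 centres with 28 × share patients each. For example, six centres with half their patients have m1 = 14:

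Var = (0.01 + 0.99/14)/6 + 0.04536/9 = 0.01345 + 0.00504 = 0.01849; SE = 0.136; 0.4/0.136 = 2.94. With 13 df, power is 78% (t), or 84% (normal).

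| EARLY centres at FID3 | Share of their patients after FID3 | EARLY patients | 5%, t | 5%, normal | 2.5%, t |
|---|---|---|---|---|---|
| 8 of 8 | all | 224 | 95% | 97% | 90% |
| 8 of 8 | half | 112 | 86% | 90% | 77% |
| 6 of 8 | half | 84 | 78% | 84% | 66% |
| 5 of 8 | one third | 47 | 59% | 66% | 46% |
| 4 of 8 | one third | 37 | 51% | 58% | 38% |

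One third corresponds, with even enrolment, to FID3 at month 6 of a 9-month period 1. If EARLY is the 9-centre arm the picture is similar: all nine centres with half their patients give 87% / 91%, and six with half give 76% / 82% (5%, t / normal).

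**The case against.** **The plan discloses the problem and has fallbacks.** This is true in part. The Data analysis plan says that late FID3 lowers power, analysis 2 is specified for that event, and analysis 3 keeps all centres. But analyses 2 and 3 are not the main analysis, and the 90% is stated without saying which analysis it serves.

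**The periods can be extended.** The power section does allow the implementation periods to be lengthened. Its trigger is low inclusion or low response, not late FID3, so enrolment could be on target with few post-FID3 EARLY patients and nothing would be triggered.

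**The loss is speculative.** This stands as a limit on size. No section says how many centres will reach FID3 or when. Six months is the length of supervision, not the time to FID3, which is judged from adherence measures and interviews. A reader might infer that most EARLY enrolment is excluded by design, or that the main analysis is underpowered by a known amount; the protocol supports neither. In the mild case (all eight centres, half their patients), 476 still gives 86% / 90% at two-sided 5%. The larger, resource-dependent non-inferiority target of 815 would also help: at 815/17 per centre, six centres with half their patients give 92% / 96%.

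**476 is an arithmetic mistake.** A reader might infer this from the 309 and 364. Without a stated alpha the inputs do not fix N, and a condensed article may leave alpha to the full plan. At two-sided 5%, 476 is too large rather than too small.

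**The surplus is a hidden reserve for fidelity losses.** It could serve as one if 5% was used and most centres reach FID3. If two-sided 2.5% with t was used, there is no reserve. The protocol says neither.

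**Conclusion.** The point holds in this form: the 90% power with 476 analysed is computed for all 17 centres contributing in full, and it is not the power of the main analysis as the protocol defines it. The size of the gap is unknown, because it depends on FID3 timing. Over the loss scenarios shown, power runs from 86% / 90% down to 51% / 58% at two-sided 5% (t / normal), and from 77% down to 38% at two-sided 2.5% with t. These figures rest on ICC 0.01, equal centre sizes of 28, EARLY as the 8-centre arm and the chosen FID3 scenarios. The 476 cannot be reproduced at two-sided 5% without an unstated alpha or allowance. That is under-specification on the large side, not a proven error.

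**What to change.** In Participant recruitment and power analysis:

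1. State the alpha, sidedness and test behind 476, and any allowance included.
2. Attach the 90% to the full-centre intent-to-implement comparison (analysis 3). If two-sided 5% with t was meant, give about 95%.
3. Give the power of the FID3-restricted main analysis over a small grid: number of EARLY centres at FID3 by share of their patients remaining in period 1.

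This is rewording and needs no extra patients. The price is a less favourable stated power for the main analysis.

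It is not necessary to require that the 476 consist only of patients eligible for the main analysis. That would conflict with step 2 and raise enrolment. Keeping 224 post-FID3 EARLY patients from all eight centres needs 224/share + 252 analysed: 551, 700 or 1148 at shares of 75%, 50% or 25%.
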